### Selection criteria

Pregnant women of African ancestry with singleton uncomplicated 11–14 week old pregnancies, who are either HIV positive for the case group or HIV negative for the control group will be recruited for the study. Pregnant women with type 2 diabetes, gestational diabetes, renal and CVDs or any critical health condition will be excluded from the study. Furthermore, data will not be collected from eligible pregnant women who have eaten, smoked or done physical exercise 6 h prior to data collection.

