### Study design and experimental plan

A prospective case–control design will be employed for this study. This will include HIV positive pregnant women on ART and HIV negative pregnant women who will serve as control. HIV positive pregnant women below 35 years of age with singleton pregnancy on ART attending antenatal clinic at  Mthatha Regional  Hospital and Nelson Mandela Academic Hospital, Mthatha will be recruited for the study and followed up during pregnancy for the presence of cardiovascular risk factors. In addition, foetal health and cardiometabolic health of the babies born to recruited women will be assessed after birth and up to 24 months after birth.

Recruited, pregnant women with known HIV positive status and who have been on ART for over 4 months will be counselled and screened for HIV to confirm their status. Thereafter, pregnant women will be assessed during antenatal visits in the first trimester (11–14 weeks), second trimester (24–26 weeks) and third trimester (35–37 weeks) for cardiometabolic risk factors including obesity, hypertension, albuminuria, insulin resistance, dyslipidaemia, oxidative stress and endothelial dysfunction. The viral load and CD4 count will be determined in the mothers at baseline and third trimester of pregnancy. A structured interviewer administered questionnaire will be used to collect data on their baseline characteristics including demographic, obstetric and family history of CVDs while anthropometric and blood pressure measurements will be performed. Placental morphometry will be assessed by ultrasound while vascular health will be assessed via pulse wave velocity (Vicorder, SMT GmbH, Germany) and endothelial function markers in blood. Microvasculature assessment will be done via retinal imaging using a retinal camera (Optomed, Finland) as previously reported [40]. Blood samples will be collected for the assessment of endothelial function markers [41], oxidative stress, lipid profile and insulin resistance markers [42] while urine will be collected for assessment of renal function. Mothers will have one post delivery follow-up for CVD risk assessment.

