Foetal health will be assessed ultrasonically in utero during the three trimester of pregnancy. Fetal health measurements will include biparietal diameter, head circumference, abdominal circumference, thoracic circumference, crown-rump length, crown-rump length and femur length. After delivery, In addition, at three, six, twelve and twenty-four months after birth, cardiometabolic risk factors will be assessed by determining BMI, blood pressure, albuminuria, oxidative stress, endothelial function as well as epigenetics markers in urine samples.

All pregnant participants will be required to fast overnight and will be asked to restrain from drinking coffee, smoking and doing exercise for 4–6 h before assessments. The study design along with the inclusion and exclusion criteria, and the series of assessments with the timeline are summarised in Figs. 1 and 2 respectively.

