#### Statistical analysis

Data analyses will be carried out using IBM statistical package for social sciences (SPSS) Version 23.0 (IBM Corp.). Armonk, NY, USA) and STATA. Data will be checked for normality using Shapiro-Wilks test and log-transformed and/or corrected for outliers when necessary. Descriptive statistics are presented as mean ± standard deviation (SD). Mean differences between groups (HIV positive pregnant women and HIV negative pregnant women) will be done using independent sample t-test. Analysis of variances (ANOVA) will be used to compare continuous variables between three or more groups. Multivariate analysis using multiple analysis of variance (MANOVA) will be used to compare continues variables for two or more independent variables (ART, HIV etc.). Chi-square test will be used to associate cardiovascular risk factors at baseline and follow-up for both mother and child. Pearson correlation will be used to assess relationship between risk factors of CVD. Linear and binomial logistic regressions will be employed to assess the risk of CVDs due to HIV and ART. A confidence interval of 95% will be taken and α = 0.05 will be considered for level of significance.

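### Foetal size is measured in visit windows 2 to 3 weeks wide, but the only two-group comparison of means that the protocol names does not adjust for gestational age at the scan

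*Protocol article*

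**What the plan says.** Foetal health in the HIV/ART environment is one of the four objectives under Aim and objectives.

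- **Outcomes.** Study design and experimental plan: "Fetal health measurements will include biparietal diameter, head circumference, abdominal circumference, thoracic circumference", followed by crown-rump length and femur length. All are measures of size.
- **Timing of scans.** Same section: "Foetal health will be assessed ultrasonically in utero during the three trimester of pregnancy". The windows in weeks are given for the women's antenatal visits: "first trimester (11–14 weeks), second trimester (24–26 weeks) and third trimester (35–37 weeks". I take the scans to happen at those visits. Selection criteria also restricts recruitment to "singleton uncomplicated 11–14 week old pregnancies".
- **Group comparison.** Statistical analysis: "Mean differences between groups (HIV positive pregnant women and HIV negative pregnant women) will be done using independent sample t-test".
- **Other methods in that section.** ANOVA is for three or more groups. MANOVA is described with ART and HIV as its factors. Regression is tied to a different question: "Linear and binomial logistic regressions will be employed to assess the risk of CVDs due to HIV and ART". No covariates are listed. The only data handling named is a normality check, log transformation and correction of outliers.

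Gestational age at the scan, z-scores and centiles are not mentioned, and no matching of the groups on gestational age is stated.

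**The concern.** A foetus scanned at the end of a window is larger than the same foetus scanned at its start. A t-test on measurements as taken counts that growth as variation between foetuses. This has two consequences.

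1. **Noise.** The SD is inflated, so a true difference is harder to detect.
2. **Possible bias.** If HIV-positive and HIV-negative women are scanned on average at different points in the window, the timing gap appears as a difference in foetal size. The groups are not randomised.

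The direction of such a bias matters. The Background cites animal work linking combination ART in pregnancy to growth-restricted offspring, so slightly earlier scans in the HIV-positive group would resemble the result that the study is looking for.

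**Working it through.** **Inputs from the protocol article.** Windows of W = 3 weeks (11–14) and W = 2 weeks (24–26 and 35–37). Sample size calculation: α = 0.05, power 0.80, d = 0.5, 64 per group before the dropout allowance.

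**Assumptions, not in the article.** Scan dates are uniform within the window. Growth is r = 0.5 to 1.0 per week, in units of the SD among foetuses of the same gestational age. The article gives no growth rate or SD, so r is also varied below.

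**Step 1: the plan's own figure.** With a two-sided α, the normal approximation gives 63 per group. The exact t calculation gives 63.8, so 64, with power 80.1% at d = 0.5. The stated 64 reproduces. It was derived from studies of vascular function and is used here only as a yardstick.

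**Step 2: loss of effect size.** A uniform window has variance W²/12, so the SD of gestational age is 0.866 weeks (W = 3) or 0.577 weeks (W = 2). Growth variance relative to between-foetus variance is r²W²/12. The effective standardised difference is d′ = 0.5 / √(1 + r²W²/12).

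| Window | r | r²W²/12 | d′ | Power at 64 per group | n per group for 80% |
|---|---|---|---|---|---|
| 3 weeks | 0.5 | 0.19 | 0.459 | 73.1% | 76 |
| 3 weeks | 1.0 | 0.75 | 0.378 | 56.4% | 111 |
| 2 weeks | 0.5 | 0.08 | 0.480 | 76.9% | 69 |
| 2 weeks | 1.0 | 0.33 | 0.433 | 68.1% | 85 |

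**Step 3: sensitivity.**

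- Slower growth, r = 0.25: power is 78% (3 weeks) and 79% (2 weeks).
- Faster growth, r = 2: power is 29% and 45%.
- Scans clustered within the window, with SD of gestational age W/6: power at r = 0.5 is 78% and 79%; at r = 1 it is 71% and 76%.
- Growth variance exceeds between-foetus variance only if r > √12/W, that is r > 1.15 (3 weeks) or r > 1.73 (2 weeks).

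**Step 4: bias if scan timing differs.** A gap of g weeks in mean gestational age adds a spurious difference of r × g within-age SD. For 2 days, g = 2/7, which gives 0.5 × 2/7 = 0.14 to 1.0 × 2/7 = 0.29 SD. With no true difference and 64 per group, the chance of a significant t-test rises from 5% to 11–23% in the 3-week window and 12–28% in the 2-week windows. If mean timing is equal, the bias is zero and only power is lost.

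**Step 5: after adjustment.** If gestational age is removed by a z-score or a covariate, d stays at 0.5 and power at about 80% with 64 per group.

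**The case against.** The strongest reply is that the article fixes a test but not the scale of the variable that goes into it. An independent-sample t-test on gestational-age z-scores would comply with the text, and converting biometry to z-scores is a detail that a condensed article may leave to the full protocol or SAP. Linear regression is also among the listed methods.

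Much of this stands. A reader might infer that the protocol commits to comparing raw foetal means. It does not say so, and it does not assign the t-test to biometry by name. However, the section does name its data-handling steps, and none of them removes gestational age. The regression it lists is directed at CVD risk. Followed as written, the section leads to an unadjusted comparison.

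Three other strong readings are not supported:

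- **That growth overwhelms the contrast.** Within the assumed range of r, growth variance is at most 0.75 of between-foetus variance. A larger r would change that, but the article gives nothing to support one.
- **That the comparison is biased.** Bias needs unequal mean scan timing. Both groups share the recruitment and visit windows, and the article neither states nor rules out a difference. The 2-day gap is illustrative.
- **That the study falls short of a promised power for foetal growth.** The 80% was set on vascular function. Nothing is promised for biometry.

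**Conclusion.** The point holds as a weakness in how the analysis is worded. It does not show that the foetal comparison will be wrong. The article schedules size measures in windows 2 to 3 weeks wide, and the only two-group comparison of means it names has no gestational-age adjustment. The noise is avoidable. Its size runs from slight (2-week windows with slow growth) to material (3-week window at 1 SD per week). Protection against a timing difference is missing in a design with no stated matching on gestational age.

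The figures rest on the assumed growth rates and uniform scan dates, and on the antenatal windows applying to the scans. Clustered scan dates or slower growth would make the loss smaller; faster growth would make it larger.

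**What to change.** In Statistical analysis, state that foetal size measures will be compared between groups in one of two ways, in place of an unadjusted t-test:

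- as gestational-age-specific z-scores, naming the reference used; or
- by linear regression on HIV/ART group, with exact gestational age at the scan (in days) as a covariate.

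State also how pregnancies are dated. The dating must be independent of the measure analysed. If crown-rump length is used for dating, that first-trimester crown-rump length should not be analysed as a growth outcome, because the adjustment would be circular.

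The same covariate can be used for the ultrasound Doppler indices under Physical/clinical measurements. No size of effect is claimed for them here.

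The cost is analysis wording, plus recording exact gestational age at each scan. Recruitment at 11–14 weeks already requires some form of dating. No extra visits or participants are needed.

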**Fig. 1 Fig1:**
[figure not shown]
Flow diagram of study design. HIV: Human immunodeficiency virus; T2D: Type 2 diabetes

**Fig. 2 Fig2:**
[figure not shown]
Study timeline and parameters. CVD: Cardiovascular disease; PWV: Pulse wave velocity; HIV: Human immunodeficiency virus

### Data collection

A structured interviewer administered questionnaire will be used for the collection of participant’s baseline characteristics and cardiometabolic risk factors (Additional file 1 - Cardiometabolic risk questionnaire). The questionnaire will contain socio-demographic information including personal data (age, sex, location and ethnicity), socio-economic status (profession, economic status, living standard). It will also contain information on maternal obstetric history, cardiometabolic health history, family history, alcohol consumption, smoking, feeding habit and physical exercise. Data will be collected using a questionnaire only at the beginning of the study.

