## Discussion

This ARTMOMSBABES study intends to investigate whether HIV-infected pregnant women on ART have a higher risk for cardiometabolic conditions and whether their offspring are borne with an increased risk for similar conditions. We are not aware of any study in sub-Saharan Africa that has utilised a longitudinal study model to assess the in utero effect of HIV/ART on cardiometabolic risk factors including vascular endothelial changes in pregnant women living with HIV and a follow up of their offspring. Existing studies have shown that the use of ART is associated with cardiovascular risk in people living with HIV [51–53] but little is known about the effect of HIV-infection and ART use in pregnant women and how these may affect the offspring exposed to both the in utero. The repeated measurements in the first, second and third trimesters of pregnancy will help to monitor changes if any in the progression of cardiometabolic risk as a result of HIV-infection and ART use in pregnancy. That is, whether there exist placental vascular changes due to ART. More so, follow-up of offspring after birth will be able to establish whether in utero expose to ART has long-term effects on the cardiometabolic health of children born of HIV-infected mothers on ART.

Findings from this study will provide information that may be helpful to develop guidelines on the use of ART and management of cardiovascular health in HIV-infected pregnant women in local health care settings. It will provide information on the cardiometabolic health of children born to HIV-infected pregnant women on ART for improved management and development of prevention policies. It will also contribute to the current global knowledge on HIV and CVD in pregnant women and children. The findings of this study may also provide an explanation and understanding of the high prevalence and early occurrence of cardiovascular risk in children especially in the South African context, as current evidence has reported increased prevalence of obesity, hypertension and other CVD risk factors in children [54–57]. These findings may also contribute to the establishment of cardiovascular disease and vascular endothelial endpoints in pregnancy which may be specific to the South African and African context but may also be useful to predict future cardiovascular events in children.

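### The only questionnaire precedes birth and no postnatal exposure is listed at the child visits, so child differences up to 24 months cannot be assigned to in utero exposure

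*Protocol article*

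**What the plan says.** Under Selection criteria, the women to be recruited are "Pregnant women of African ancestry with singleton uncomplicated 11–14 week old pregnancies". Under Data collection, one questionnaire covers, among other things, "family history, alcohol consumption, smoking, feeding habit and physical exercise", and its timing is explicit: "Data will be collected using a questionnaire only at the beginning of the study".

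Under Study design and experimental plan, the children are seen repeatedly: "at three, six, twelve and twenty-four months after birth, cardiometabolic risk factors will be assessed". The means are given as "determining BMI, blood pressure, albuminuria, oxidative stress, endothelial function as well as epigenetics markers in urine samples". HIV markers are placed in the mothers: "The viral load and CD4 count will be determined in the mothers at baseline and third trimester of pregnancy".

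The Discussion states that follow-up of the offspring "will be able to establish whether in utero expose to ART has long-term effects" on the children's cardiometabolic health. Its closing paragraph again presents possible cardiovascular risk in the children as the consequence of exposure before birth. The Statistical analysis section plans linear and logistic regression for risk due to HIV and ART and names no postnatal covariate. The limitations in the Discussion cover location and ethnicity, length of follow-up and the choice of cut-offs, but not postnatal exposure.

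**The concern.** The children's outcomes are measured 3 to 24 months after birth, while the only exposure history is taken in the first trimester. Between the two, the groups may come to differ in infant feeding, in antiretroviral drugs given to the infant and in the child's own HIV status. It is plausible that these depend on the mother's HIV status and affect growth, blood pressure and oxidative-stress markers, though the documents say neither.

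If so, a difference between exposed and unexposed children combines prenatal and postnatal effects, and the described data offer no way to tell them apart. What is at stake is the study's most far-reaching statement, that follow-up can establish a lasting effect of in utero ART exposure. Feeding history that is not taken at the time is hard to recover, and no analysis plan can use a variable that was never recorded.

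A smaller matter follows from the same sentence. Smoking and alcohol are asked about once, although they can change later in pregnancy and bear on the in utero environment itself.

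**Working it through.** **Timing**

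- Questionnaire: at study start, and enrolment is at 11–14 weeks.
- Last antenatal visit: 35–37 weeks (Study design and experimental plan). The interval without a repeat questionnaire before that visit is 35 − 14 = 21 to 37 − 11 = 26 weeks.
- First listed postnatal assessment of the child: 3 months after birth.

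The feeding item in the questionnaire is therefore answered before the child exists. It can only describe the mother's own habits.

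**What the article describes for each factor**

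| Factor | Could the enrolment questionnaire record it? | Listed at the child visits? | Other source in the article |
|---|---|---|---|
| Infant feeding | No | No | None described |
| Smoking and alcohol later in pregnancy | No | Not applicable | None described |
| Infant antiretroviral drugs | No | No | None described |
| Child HIV status | No | No | Unclear: the laboratory section lists viral load without separating mother from child |

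**The plan's own figure**

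The only design figure is 64 per group (Sample size calculation: α = 0.05, power 0.80, d = 0.5). By normal approximation, n = 2 × (1.960 + 0.842)² / 0.5² = 62.8, that is 63. The two-sided t-test gives 63.77, that is 64. The figure reproduces, and 64 × 1.25 = 80 gives the recruited number. The present point does not depend on it.

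**Illustration of size (assumed values, none from the documents)**

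Part of the group difference that comes from an unrecorded factor, in SD = (difference between groups in its prevalence) × (its effect in SD).

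- Low: 0.20 × 0.20 = 0.04 SD.
- High: 0.40 × 0.40 = 0.16 SD.
- Against d = 0.5: 0.04 / 0.5 = 8% and 0.16 / 0.5 = 32%. This is only a yardstick, because d was taken from studies of vascular function in HIV patients, not from child BMI or blood pressure.

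If the true in utero effect is zero, the chance that a two-sided 5% t-test shows a group difference, which would then be read as an in utero effect, is:

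| Difference from the factor | 60 per group (80 × 0.75) | 64 per group | 80 per group |
|---|---|---|---|
| 0.02 SD (0.1 × 0.2) | 5.1% | 5.1% | 5.2% |
| 0.04 SD (0.2 × 0.2) | 5.5% | 5.6% | 5.7% |
| 0.15 SD (0.3 × 0.5) | 12.9% | 13.4% | 15.6% |
| 0.25 SD (0.5 × 0.5) | 27.4% | 28.9% | 34.9% |

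The effect runs from negligible to material, and the data as described could not show which applies.

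**The case against.** Four objections carry weight.

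- **The sentence limits one instrument, not all data collection.** A reader might infer that infant antiretroviral exposure and child HIV status cannot be taken into account at all. The documents do not support that. Both can come from clinic records or laboratory tests, the laboratory section is ambiguous about who is tested, and Fig. 2 and the questionnaire file are not shown. The article is also a condensed account. For these two items one can say only that it describes no collection of them. For infant feeding and later smoking or alcohol the point is firmer, because the plan positively rules out a later questionnaire and describes no other source.
- **These factors lie downstream of maternal HIV status.** A reader might also infer that the comparison of exposed with unexposed children is confounded by them. That does not follow. As consequences of maternal HIV/ART they are part of its total association with child health, and leaving them unadjusted does not bias that total. They matter when a purely prenatal effect is claimed.
- **Adjustment may not achieve the separation.** If infant antiretroviral drugs are given essentially only to exposed children, they cannot be told apart from group membership however well recorded. Restricting to uninfected children conditions on something that happens after exposure. Adjustment therefore belongs in a secondary analysis.
- **The stated aim speaks of association, and the strong wording is in the Discussion.** This is true, and the closing paragraph is hedged. But the statement in the Discussion that follow-up can establish a long-term in utero effect is unqualified, and it is the use to which the child data are to be put.

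**Conclusion.** The concern holds in this form: the only questionnaire comes before birth, no postnatal exposure is listed among the child assessments, and the described data cannot support the attribution of child differences at 3 to 24 months to in utero exposure. The fault lies in the gap between the data described and the conclusion announced, not in the group comparison as such.

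The size is unknown from the documents. The 0.04–0.16 SD rests wholly on assumed prevalence differences and effects, and its lower end would hardly matter. The conclusion also assumes that postnatal factors follow maternal HIV status, which is plausible but not stated. The change is worth making because it is cheap and because feeding history cannot easily be reconstructed later.

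**What to change.** 1. **Reword the Discussion (essential).** In both places, speak of association with perinatal HIV/ART exposure, and add unseparated postnatal exposure to the limitations.
2. **Data collection section.** Delete the restriction of the questionnaire to study start. Add a short REDCap form at the existing antenatal visits (smoking, alcohol, changes in ART) and at the existing child visits (feeding mode and duration; infant antiretroviral drugs and HIV test result, both copied from routine records).
3. **Analysis.** Keep the group contrast without adjustment for postnatal factors as the total perinatal HIV/ART association. Add a secondary analysis that accounts for feeding and restricts the exposed group to HIV-exposed uninfected children. State there that infant antiretroviral exposure may not be separable from group.

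The cost is a few minutes of nurse time per visit and a less specific conclusion. No new visit, procedure or test is needed.
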